## Discussion

This study protocol documents the two-arm cluster randomised controlled trial with baseline and post-assessment for MindMatters primary schools, a holistic school-based intervention to promote mental health in school children. While the overall intervention targets children and adolescents in primary and secondary schools, this study focuses on the primary school module, for which there is no previous evidence. Reductions in mental and behavioural problems in children will be the primary outcomes, preceded by improvements in knowledge and social-emotional skills, as well as organisational improvements such as classroom climate, classroom disruption and organisational commitment. In addition, we expect these intervention effects to have a positive long-term impact on pupils’ educational outcomes.

While the effectiveness of highly standardised behavioural modification interventions is well documented, there is still an evidence gap for complex intervention programmes that take into account environmental and organisational determinants. This problem has also been labelled as ‘inverse evidence law’ [23], and the results of this study aim to contribute to strengthen the evidence base for holistic interventions on school (mental) health promotion. Its strengths can be seen in the study design (a two-arm cluster randomised controlled trial), which has a comparatively high internal validity. By interviewing younger children, the study focuses on a target group that has received little attention so far; to date, parents or teachers have mostly been interviewed, but not the children themselves [46]. Younger children’s own perspectives can provide valuable information for assessing mental health as part of a multi-informant approach [47]. In addition, innovative methods are used: pupils are surveyed using tablet computers that guide them through the questionnaire in the classroom in a structured and visually appealing way. The inclusion of pictorial representations of the questions may improve the reliability of self-reports in younger children [48]. It should also be emphasised that the study links several indicators of implementation fidelity with intervention effectiveness and will also help to shed more light on the relationship between health and educational attainment. Evidence from the Wales-wide School Health Research Network suggests that school health policies and curriculum practices are associated with educational attainment at age 14, particularly in disadvantaged schools [49]. However, as emphasised by Langford et al. [13] in their Cochrane review, the available evidence is scarce and does not allow conclusions to be drawn about the effectiveness of interventions on school health promotion. Evidence of such effects would also confirm the conceptual approach of the Good Healthy School [18]. As health is not a mandatory part of the school curriculum or cross-curricular activities in many countries, evidence would provide important arguments for establishing (mental) health in everyday school life. Finally, it should be noted that the results of the trial also aim at helping funding institutions and decision-makers in allocating resources.

The main limitation of this study is the assessment via self-reports. There is an increased risk of systematic bias, such as recall bias. Especially in younger children, challenges such as limited language and cognitive abilities or comprehension difficulties must be taken into account [50], although self-reports have previously been shown to be reliable and valid measures of mental well-being in adolescents. In addition, the power calculation was made a priori without information on the ICC estimate for mental disorders in children. Post hoc, the ICC for the SDQ could be determined from the pilot data and it was found that the ICCs ranged from *p* = 0.03 (hyperactivity) to *p* = 0.07 (behavioural problems with peers), indicating a severe underestimation of the ICCs for the SDQ. Furthermore, the SDQ might not be an adequate proxy for mental disorders, as it includes, for example, items for classroom disruption and prosocial behaviour. Although the trial might therefore not be suitably powered to detect small intervention effects, type I error inflation might be cushioned by the large number of clusters at the classroom level.

Also, as participation is voluntary, non-compliance could become an issue. Teachers are expected to teach the prepared modules and excercises independently of their teaching responsibilities and may find this an additional burden. These classes may discontinue participation in MindMatters early. Another limitation to the implementation of the intervention is the significant additional burden placed on schools by the Corona pandemic. As health promotion is not legally anchored in schools, this could lead to limited resources being invested in school health interventions [51]. As a result, a certain selection bias in school participation cannot be ruled out. Finally, this study is conducted in three German federal states, and conclusions cannot be directly transferred to other federal states due to the differences in the education systems.

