**Fig. 1 Fig1:**
[figure not shown]
SPIRIT figure

Primary schools are eligible to participate if (1) they are from one of the three federal states (North Rine-Westphalia, Rhineland-Palatinate, Schleswig–Holstein), (2) they have not implemented the MindMatters intervention in the past and (3) they agree to be assigned to either the intervention or control group. After enrolment, eligible schools will be randomly assigned 1:1 to either the intervention or control group using the Microsoft Excel random number function, with randomisation stratified by subgroups: federal state, school size, social gradient and level of activity in school health promotion. Within the subgroups, each school will be assigned a random number, with the proviso that, for example, schools with large random numbers will be assigned to the intervention group and schools with small random numbers will be assigned to the control group. Randomisation and communication with schools will be carried out by the investigators. Schools will be informed individually by e-mail of the outcome of the group allocation. Data will be collected at baseline and again 18 months after the start of the intervention, including the perspectives of pupils and teachers (both baseline and post-test) as well as parents (post-test only). While the MindMatters intervention is implemented in the intervention schools according to defined criteria, no intervention is implemented in the control schools. The trial flow of the evaluation study is shown in Fig. 2. The trial has been approved by the Ethical Review Board of Fulda University of Applied Sciences (Nr. 3.1.9.2), the Ministries of Education in Rhineland-Palatinate and Schleswig–Holstein, and registered with the German Clinical Trials Register (DRKS00023762).

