### Sample size calculation

In this study, schools represent the intervention clusters in which classes and pupils are nested. The power analysis relates to the individual pupil level, taking into account the cluster effect by including the intraclass correlation (ICC). There is no ICC estimate for mental disorders in the target age group, but it is estimated to be rather low compared to substance use or risky behaviour and is therefore set at *p* = 0.01 for the power analysis [22]. While the medium effects can be expected at the level of knowledge for primary school pupils (*d* = 0.5), small effects (*d* = 0.1 to 0.3) are assumed at the level of competence due to the short study period. Given the most recent findings on the prevalence, it is expected that the prevalence of mental health problems in the intervention group will be at most four percentage points lower than in the control group at the post-test.

Assuming an alpha level of 5% and a statistical power of 0.80, the estimated sample size is 2066 (with equal allocation to both groups, i.e. 1033 pupils in the intervention group and 1033 in the control group, https://www.sealedenvelope.com/power). Taking into account an intra-class correlation of 0.01 and a number of approximately 15 pupils per class with parental consent and actually present on the day of the survey, the required total sample size increases as follows: (1 + (15 − 1) × 0.01) × 2066 = 2355. Based on previous studies in primary school education, an attrition rate of about 10% is calculated for the pre-post survey at the pupil level across the different measurement points, so that a total sample of 2615 pupils from 174 classes is required for the baseline test. It is planned to implement this with a total of 40 participating primary schools (20 in the intervention group and 20 in the control group).

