Statistical analyses will be performed using the latest version of STATA (Stata Corp., College Station, TX, USA). The main analysis will consist of a multilevel regression in which the primary outcomes are predicted at the pupil level using group status (intervention versus control group), controlled for baseline condition. Group status will be included in the model as a fixed effect and a random intercept will be provided for the cluster variables (study region, school, class). Furthermore, all variables with differences between the intervention and control group at baseline will be included in the model. Further mediation analyses will investigate which mediating mechanisms can be identified. It is assumed that the change in mental health outcomes is caused by improvements in proximal (i.e. direct and class/organisational) outcomes. This requires that the group status (i.e. the intervention) is correlated with the proximal outcomes and that the proximal outcomes are significantly related to the distal outcomes. Mediation effects will be examined using the Baron and Kenny partial correlation analysis approach and structural equation models [44, 45]. Moderator analyses will also examine which school-level factors (e.g. size, social gradient) are associated with or influence the impact of MindMatters. Moderator effects are tested using interaction terms in the regression model. The analysis will first be conducted according to the intention-to-treat principle and additionally compared with a per-protocol analysis. Analysis sample 1 includes all those for whom data are available at both measurement points (complete case analysis, as randomised). Analysis sample 2 includes all those reached at baseline (ITT as randomised). Analysis sample 3 includes all those with data available at both measurement points, and schools without intervention are included in the control group. Multiple imputation is used for missing values. To ensure the methodological quality of all analyses, statistical advice is provided by an independent institute.

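### The many classes cannot cushion type I error: 40 schools are randomised, and the underestimated ICC costs power instead

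*Protocol article*

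**What the plan says.** Under Study design, "eligible schools will be randomly assigned 1:1 to either the intervention or control group". The Sample size calculation says that "schools represent the intervention clusters in which classes and pupils are nested" and plans 40 schools, 20 per arm. The same section states that "a total sample of 2615 pupils from 174 classes is required for the baseline test". Its design effect uses an ICC of 0.01 and 15 pupils per class.

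The statistical analysis section plans a multilevel regression with group status as a fixed effect and random intercepts for study region, school and class. Variables that differ between the groups at baseline are added.

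The limitations part of the Discussion reports pilot ICCs for the SDQ of 0.03 to 0.07, calls the planning value a severe underestimate, and accepts that small effects may be missed. It then adds that "type I error inflation might be cushioned by the large number of clusters at the classroom level".

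**The concern.** Arm is constant within a school. Every class in a school carries the same assignment, so further classes sharpen the estimate of that school's mean but add no independent comparison between arms. The sentence locates the protection at a level where nothing was randomised, against the protocol's own definition of the cluster.

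It also mixes two kinds of error. The admitted fault is a planning ICC that was too small. That makes the trial too small for its target power. Type I error depends on whether the fitted model allows for school-level variation and which reference distribution is used, not on the ICC assumed in advance.

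At stake is the only reassurance on error control that follows the admission of low power. A reader who accepts it would take the evidence to rest on 174 units when it rests on 40.

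**Working it through.** **Inputs from the protocol.** 40 schools, 174 classes, 2355 pupils analysed, 2615 at baseline, alpha 5%, planning ICC 0.01, pilot ICCs 0.03 to 0.07. Not given: the base rates, the level (school or class) of the pilot ICCs, the estimation method and the reference distribution. These are assumed below and shown as ranges.

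**The plan's own figures.** No type I error rate is stated, so only the sample size can be reproduced.
- With an assumed 14% against 10%, two-sided: (1.960 + 0.842)² × (0.14 × 0.86 + 0.10 × 0.90) / 0.04² gives 1033 per arm, 2066 in total, as stated.
- Design effect: 1 + 14 × 0.01 = 1.14, and 1.14 × 2066 = 2355, as stated.
- Attrition: 2355 / 0.9 = 2617, against 2615 stated; 2615 / 15 = 174 classes.

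**Degrees of freedom.** Between schools: 40 − 2 = 38, critical t = 2.024. Between classes, if they were independent: 174 − 2 = 172, critical t = 1.974. Normal reference: 1.960.

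**Size when school is modelled, as planned.**
- Unbiased variance, normal reference: 2·P(t₃₈ > 1.96) = 5.7%. With 34, 30 or 20 df left after covariates or strata: 5.8%, 5.9%, 6.4%.
- Maximum likelihood, normal reference: the between-school variance is divided by 40 instead of 38, so the size is 2·P(t₃₈ > 1.96·√(38/40)) = 2·P(t₃₈ > 1.910) = 6.4%.
- The same with five or six school-level covariates (an assumed number): 33 df gives 8.4%, 32 df gives 8.9%.
- Simulation of 40 schools × 59 pupils, 200,000 trials at each of ICC 0.01, 0.03 and 0.07: maximum likelihood with z 6.2–6.3%, REML with z 5.7%, REML with t on 38 df 4.9–5.0%.

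**Size if classes were the independent units and school were ignored.** With m = 2355/174 = 13.5 pupils per class and M = 2355/40 = 58.9 per school, the variance that a class-level analysis assumes is proportional to 1 + (m − 1)(ρ_school + ρ_class). The true variance adds (M − m)·ρ_school. For ρ_school = 0.01 and ρ_class = 0 these are 1.125 and 1.579, so the size is 2·P(Z > 1.96/√(1.579/1.125)) = 9.8%. Null simulations with 40 schools and 174 classes (6,000 runs per setting):

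| School ICC | Class ICC | Class test, 172 df | School test, 38 df |
|---|---|---|---|
| 0 | 0.03 | 4.7% | 4.5% |
| 0.01 | 0 | 9.4% | 4.7% |
| 0.01 | 0.02 | 8.9% | 5.1% |
| 0.03 | 0 | 15.9% | 4.7% |
| 0.03 | 0.02 | 14.6% | 4.6% |
| 0.035 | 0.035 | 15.4% | 5.0% |
| 0.07 | 0 | 24.4% | 4.9% |

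The 174 classes keep the error at 5% only when there is no school-level variance. The school-level test keeps it throughout.

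**What the low ICC does cost.** With 2355 analysed and the assumed 14% against 10%, power at ICC 0.03 to 0.07 falls from the planned 80% to about 71% to 57% if the ICC acts at class level (m = 15), and to about 44% to 26% if it acts at school level (m ≈ 59). The class-level figures already credit the trial with all its classes.

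**The case against.** The strongest reply is that the main safeguard is already planned: the analysis section puts school in the model as a random intercept, and the sample size section names schools as the clusters. The disputed sentence is hedged, sits in a limitations paragraph and sets no analysis rule. The same paragraph openly admits the ICC problem. All of this stands, and it limits the size of the point.

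Three stronger readings are tempting and should not be drawn.

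- A reader might infer a true error rate of 9% to 24%. That needs an analysis without school, which the plan contradicts.
- A reader might take 8.4% to 8.9% as the expected rate. That combines maximum likelihood, a normal reference and five or six school-level covariates. The protocol states none of these: it says that "Statistical analyses will be performed using the latest version of STATA", which fixes neither an estimator nor a test distribution, and it gives neither the number nor the level of the added variables.
- A reader might fault the article for naming no small-sample method. Such detail is commonly left to a fuller plan, so its absence is not the point here.

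Nor do the documents show that the analysts will be misled.

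What the reply does not rescue is the sentence itself. Once schools differ at all, the number of classes does not supply the protection claimed under any modelling choice.

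**Conclusion.** The statement is wrong and should not stand. Error control for the intervention effect rests on 40 schools and at most 38 degrees of freedom, less any school-level covariates. The underestimated ICC is a loss of power.

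Under the planned model the remaining inflation is modest and conditional: about 5.7% with a normal reference, about 6.4% with maximum likelihood as well, more if several school-level covariates are fitted, and none of note with a t reference on 38 degrees of freedom. The conceptual error is certain. These sizes depend on an estimator and reference distribution that the article does not state, and the power figures depend on assumed base rates and on the unstated level of the pilot ICCs.

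**What to change.** Delete the sentence, or replace it with one saying that the underestimated ICC reduces power and that control of type I error rests on the 40 randomised schools.

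Base inference on the intervention effect on school-level degrees of freedom:
- For continuous SDQ scores, use REML with a small-sample correction, or a t reference with 38 degrees of freedom less the number of school-level covariates. Satterthwaite and Kenward–Roger degrees of freedom are estimated from the data and can drift upwards when the school variance is estimated near zero, so the fixed between-school value is the safer ceiling.
- For any binary outcome, such as the prevalence used in the sample size, REML with Kenward–Roger does not carry over. Use a t reference with between-school degrees of freedom, or analyse school-level summaries.

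The school random intercept is already planned and needs no change. The cost is one sentence and a model option. Intervals widen by about 3% to 4% (2.024/1.960 = 1.03; 2.04/1.96 = 1.04). Recruitment is complete according to Trial status, so this affects analysis and reporting only.

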### Trial status

Protocol version 2, 6 October 2023. Recruitment of schools started in May 2021 and was completed in January 2022, with data collection continuing until September 2023. Due to the Corona pandemic, the data collection process had to be adapted several times.

## Data Availability

Publications will be made open access. The datasets generated during the current study will not be made open access but may be made available on request to the principal investigators ([name]) and according to the ethical approval. At present, there are no plans to use the data in ancillary studies, and no consent has been obtained from participants.

## Abbreviations

COAKTIV: Cognitive Activation in the Classroom: The Orchestration of Learning Opportunities for the Enhancement of Insightful Learning in Mathematics
COMMIT: Commitment-Skalen [Commitment Scales]
COPSY: Corona und Psyche [Corona and Mind]
CRCT: Cluster-randomised controlled trial
*d*: Cohen’s *d* effect size
DALY: Disability-adjusted life years
FASS: Fragebogen zur Arbeitssituation an Schulen [questionnaire on the working situation in schools]
FEESS: Fragebogen zur Erfassung emotionaler und sozialer Schulerfahrungen [questionnaire for the assessment of emotional and social school experiences]
GBD: Global Burden of Disease
GHQ-12: General Health Questionnaire
HoL: Health-oriented leadership
ICC: Intraclass correlation
IFT Nord: Institute for Therapy and Health Research North
KESS: Kompetenzen und Einstellungen von Schülerinnen und Schülern [competencies and attitudes of pupils]
NCD: Non-communicable diseases
NEPS: National Educational Panel Study
PISA: Programme for International Student Assessment
QuaSSU: Qualitätssicherung in Schule und Unterricht [quality assurance in school and teaching]
SDQ: Strengths and Difficulties Questionnaire
SEL: Social-emotional learning
SEP: Selbstevaluationsportal [self-evaluation portal]
SPIRIT: Standard Protocol Items: Recommendations for Interventional Trials
SSPESH: Survey of School Promotion of Emotional and Social Health
STATA: Statistical Software for Data Science
USG: Umsetzungsstand schulischer Gesundheitsförderung [implementation status of school health promotion]
VPN: Virtual private network
